## Abstract

**Objective::**

The objective of this present research is to evaluate the effect of the intervention of enhancing quality of life in patients in patients with advanced lung cancer.

**Methods::**

Our research is carried out as a randomized clinical trial which will be implemented from December 2020 to October 2021. It was approved by the Ethics Committee of People's Hospital of Chengyang District (03982790). This study includes 90 patients with advanced lung cancer. Patients diagnosed at our oncology clinic are eligible if they are diagnosed within 8 weeks of a novel diagnosis of stage 3 or stage 4 lung cancer. Patients with hepatic insufficiency, renal failure, and respiratory and heart failure, as well as a series of severe mental illness are excluded from our research. Patients are divided randomly into the intervention group and control group, each group is assigned 45 patients. Through utilizing functional assessment of cancer therapy–lung, the measurement of life quality is conducted. And the measurement of mood is carried out with Hospital Anxiety and Depression Scale.

**Results::**

Table 1 indicates the patient's life quality and Hospital Anxiety and Depression Scale in both groups.

**Conclusion::**

Enhancing quality of life in patient intervention may be beneficial to improve the life quality in advanced lung cancer patients.

Trial registration: The protocol was registered in Research Registry (researchregistry6243)

## Introduction

1

Lung cancer is the main cause of cancer in the world; approximately 1.6 million patients are diagnosed with lung cancer every year.^[1,2]^ It is the most familiar cause of deaths associated with cancer, with 1.3 million people dying from the disease each year, accounting for 1/5 of cancer deaths. Most lung cancers can be divided into small-cell lung cancer or non-small cell lung cancer. At the time of diagnosis, most patients have metastatic cancer or locally advanced cancer that is incurable, with a 5-year mortality rate of 85% to 90%.^[3]^ The treatment method for lung cancer is determined by the type of lung cancer, the disease stage, and the performance status of patients.^[4]^ The treatment methods involve radiation therapy, chemotherapy, surgical resection, palliative care as well as targeted therapy.^[5,6]^

The goal of treatment is to improve the life quality and prolong the life of patients with advanced lung cancer, or both. Nevertheless, due to poor functional status, many patients have limited treatment options. Many factors may lead to low functional status, involving comorbidities, high tumor burden, and older age.^[7]^ For the cancer progression, its direct effects include weight loss, shortness of breath, pain, and fatigue, together with some indirect influences of the cancer treatment, can accumulate to further deterioration in the life quality, sustained loss of physical health, and a decline in levels of physical activity.^[8,9]^ In patients with advanced lung cancer, the palliative care may have the greatest benefit, which may be due to the low life quality and heavy burden of symptoms of advanced lung cancer patients.^[10]^

The intervention of enhancing quality of life in patients (EQUIP) is a kind of supportive nursing intervention for the advanced lung cancer patients, which is dominated by nurses. It consisted of four educational sessions, led by a research nurse, on how to deal with the prevalent lung cancer symptoms, that is, worry, breathlessness, and fatigue. The objective of this present research is to evaluate the effect of the intervention of EQUIP in the advanced lung cancer patients.

## Methods

2

### Study design

2.1

This experiment is implemented as the randomized clinical study which will be conducted from December 2020 to October 2021. After obtained approval from the Ethics Committee of People's Hospital of Chengyang District (03982790), we registered it in research registry (researchregistry6243). This study includes 90 patients with advanced lung cancer. With the use of the random number table, all patients will be assigned the random number, and the distribution results will be hidden in the random envelope. All the patients are randomly assigned to the control and intervention group, each group is assigned 45 patients.

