### Inclusion of exclusion criteria

2.2

Patients diagnosed at our oncology clinic are eligible if they are diagnosed within 8 weeks of a novel diagnosis of stage 3 or stage 4 lung cancer. Patients with hepatic insufficiency, renal failure, and respiratory and heart failure, as well as a series of severe mental illness are excluded from our research.

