### Statistical analysis

2.5

All the data can be recorded into the software of Microsoft Excel 2013, and the analysis of all the data is carried out through utilizing the software of IBM SPSS Statistics for Windows, version 20 (IBM Corp., Armonk, NY). All the data are represented via the proper characteristics, for instance, median, mean, and percentage. The categorical variables and continuous variables are respectively analyzed using independent *t*-tests and χ^2^-tests. *P* value less than .05 indicates that there is statistical significance.

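### Stage balance in 90 patients is left to chance and not corrected: no stratification is described and the stated tests are unadjusted

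*Protocol article*

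**What the plan says.** Study design (2.1) gives the allocation in three statements. The sequence comes from a table: "With the use of the random number table, all patients will be assigned the random number". Concealment is by envelope: "the distribution results will be hidden in the random envelope". The arm sizes are fixed: "All the patients are randomly assigned to the control and intervention group, each group is assigned 45 patients". Table 1 repeats 45 in each column head. Neither stratification nor blocking is mentioned.

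The eligibility section (2.2) admits patients if "they are diagnosed within 8 weeks of a novel diagnosis of stage 3 or stage 4 lung cancer", so two stages enter one comparison. The Introduction says: "The treatment method for lung cancer is determined by the type of lung cancer, the disease stage, and the performance status of patients". It also lists high tumour burden among the causes of poor functional status, and links cancer progression and its treatment to falling quality of life.

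Statistical analysis (2.5) states: "The categorical variables and continuous variables are respectively analyzed using independent *t*-tests and χ^2^-tests". Read literally, that sentence pairs the tests with the wrong variable types, which is a separate matter. What counts here is that both are two-sample comparisons without covariates.

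**The concern.** The outcomes are quality of life and mood. On the article's own account, stage bears on the treatment a patient receives, and disease progression and treatment bear on quality of life. Stage is known for every patient at entry, because eligibility depends on it. Even so, the article uses it neither in the allocation nor in the analysis.

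In a trial of 90, a visible difference in stage mix between arms is quite possible. If it arises, the stated analysis cannot separate its contribution from that of the intervention in the observed estimate, and the report would have no pre-planned answer to a reader who points to the imbalance. Adjusting only after the imbalance has been seen is weaker than planning it, because the choice then depends on the data.

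**Working it through.** **Inputs.** Total 90 and arms of 45 and 45 (Study design); 45 + 45 = 90, so the article's own figures agree. It gives no sample-size calculation to reproduce. Two stages are eligible (section 2.2). The number of stage 4 patients, K, is not given. I assume 50 to 70% (K = 45 to 63) and show 30 to 80% for sensitivity. The 15-point threshold is a convention chosen for illustration, so 10 and 20 points are shown too.

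**Model.** With the split fixed at 45:45 and no stratification, the number X of stage 4 patients in the intervention arm is hypergeometric: 45 drawn from 90, of whom K are stage 4. The control arm has K − X, so the difference in stage 4 share is |2X − K| / 45.

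**Spread.** For K = 54 (60%), the SD of X is √(45 × 0.6 × 0.4 × 45/89) = 2.34. The SD of the difference is 2 × 2.34 / 45 = 0.104, or about 10 percentage points.

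**Tail probability.** A difference of at least 15 points needs |2X − K| ≥ 0.15 × 45 = 6.75. As 2X − K has the parity of K, this means at least 7 when K is odd and at least 8 when K is even.

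- K = 45: X ≤ 19 or X ≥ 26, so 2 × 0.1028 = 0.206.
- K = 54: X ≤ 23 or X ≥ 31, so 2 × 0.0658 = 0.132.

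| Stage 4 share (K) | ≥ 10 points | ≥ 15 points | ≥ 20 points |
|---|---|---|---|
| 30% (27) | 0.358 | 0.167 | 0.065 |
| 40% (36) | 0.282 | 0.132 | 0.052 |
| 50% (45) | 0.399 | 0.206 | 0.091 |
| 60% (54) | 0.282 | 0.132 | 0.052 |
| 70% (63) | 0.358 | 0.167 | 0.065 |
| 80% (72) | 0.187 | 0.063 | 0.016 |

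Because of parity, round shares do not show the full range. Over every K from 45 to 63, the 15-point probability runs from 0.110 (K = 62) to 0.206 (K = 45).

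**Consequence for the estimate.** If the mean outcome differs by D between stages, an imbalance of 7 patients (7/45 = 0.156) shifts the unadjusted difference between arms by 0.156 × D. The article gives no value for D, so this cannot be turned into scale points.

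**With stratification.** As an illustration, permuted blocks of 4 within each stage hold the arms to a difference of at most 2 patients per stage. If both stages are off by 2 in the same direction, the totals are 47:43.

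**The case against.** The strongest reply is that unstratified randomisation of 90 patients is a legitimate design. The t-test and chi-square test keep their type I error, because chance imbalance in stage is part of the variation they allow for. This stands. Stage imbalance here is not confounding in the sense of systematic bias.

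Second, the Introduction says that stage affects treatment, not that it predicts scores on these two instruments, and it names cancer type and performance status alongside stage. This stands in part. The size of any effect of stage on outcome is unknown. But stage is the factor by which the eligibility criteria define the population, and it is recorded for everyone at entry, which makes it the natural first choice.

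Third, an article may leave stratification factors and covariates to a fuller document. That is fair for what is silent. The analysis is not silent, however: it names the tests, and they are unadjusted.

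Fourth, the figures depend on an assumed stage mix and a chosen threshold, and differences of 20 points or more are uncommon (about 2 to 9% over the mixes tabulated). This also stands, and it limits the weight of the point.

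A reader might go further and infer that a random number table will seldom yield exactly 45:45, or that the split must be forced by closing a full arm, which would make late allocations predictable. The article supports neither. It does not say that allocation is unrestricted or that an arm is closed. Fixing the sizes ("each group is assigned 45 patients") is itself a restriction, and ranking 90 random numbers and giving 45 to each arm produces that split every time.

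**Conclusion.** The point holds as a recommended improvement, not as an error that invalidates the trial. As described, the design leaves stage balance to chance, and the stated tests do not correct for it. With a fixed 45:45 split and an assumed 50 to 70% stage 4, the chance of a difference of at least 15 percentage points is about 11 to 21%. Over the wider range of 30 to 80% it is about 6 to 21%. The loss is in precision and in how convincingly a result can be defended. Its size in outcome units depends on how strongly stage affects the scores, which the article does not give.

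**What to change.** 1. Generate the whole allocation list before enrolment, in permuted blocks of randomly varying size, stratified by stage (3 v 4), and prepare one sequentially numbered set of sealed envelopes per stratum.
2. Replace the unadjusted t-test for the continuous scores with a regression or ANCOVA that has arm and stage as terms, stated before any outcome data are seen. The two steps belong together: an unadjusted test after stratified allocation does not use the precision that stratification gains.
3. Describe the arm sizes as approximately 45 each.

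The cost is a new list, a second envelope set and a final split that may differ from 45:45 by a patient or two. Precision hardly suffers from that: relative efficiency, 4 × n1 × n2 / 90², is still 0.988 at 50:40. If enrolment has already begun, the covariate adjustment can still be adopted with no change to recruitment.

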### Inclusion of exclusion criteria

2.2

Patients diagnosed at our oncology clinic are eligible if they are diagnosed within 8 weeks of a novel diagnosis of stage 3 or stage 4 lung cancer. Patients with hepatic insufficiency, renal failure, and respiratory and heart failure, as well as a series of severe mental illness are excluded from our research.

### Intervention in both groups

2.3

In the control group and the intervention group, the patients are given routine care, that is, access to all palliative and oncology treatment services. Furthermore, the EQUIP intervention group undergoes four face-to-face meetings with the nurse. All courses are carried out by the same research nurse with the experience of community palliative care and the registered nurse qualification. The research nurse only participates in the implementation of EQUIP intervention; the evaluations of patient reports are managed via a separate study coordinator who is unaware of the allocation of two groups. The EQUIP courses arrangement is consistent with the existing outpatient chemotherapy or clinic visits time, so as to minimize the inconvenience to the patients. The focus of these courses is to equip the patients with the strategies and skills to deal with pervasive symptoms of lung cancer patients. This content includes the following aspects:

(1)Fatigue: introducing the patients to the nonpharmacological treatment of fatigue, containing maintaining activity vitality and rhythm;(2)Breathlessness: introducing nonpharmacological treatment of breathlessness to the patients, involving relaxation techniques and breathing, fan therapy, and mindfulness;(3)Worry: introducing the psychobehavioral strategies to the patients to deal with worry; and(4)Recap of the former sessions. After ending each session, the patients are given a 1-page summary of content.

### Data collection

2.4

With the functional assessment of cancer therapy–lung, the measurement of life quality can be conducted.^[11]^ The 36-item tool measures emotional, physical, social, emotional, functional health and the symptoms specific to lung cancer. With Hospital Anxiety and Depression Scale, the measurement of mood is carried out.^[12]^ This 14-item tool consists of 2 subscales for depression and anxiety. This is a kind of categorical scale, and cut-off scores for each subscale are as follows: 0 to 7 represents normal, 8 to 10 represents mild, 11 to 14 represents moderate, and 15 to 21 represents severe.

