## Results

3

Table 1 indicates the patient's life quality and Hospital Anxiety and Depression Scale in both groups.

**Table 1 T1:** Patient's life quality and HADS in both groups.

Outcomes	Study group (n = 45)	Control group (n = 45)	*P* value
Physical well-being			
Social well-being			
Emotional well-being			
Functional well-being			
Overall quality of life			
Anxiety subscale			
Normal			
Mild			
Moderate			
Severe			
Depression subscale			
Normal			
Mild			
Moderate			
Severe			

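### HADS anxiety and depression are declared categorical and laid out as four severity bands, although each subscale is a 0-21 score; comparing bands instead of scores would cost substantial power with 45 patients per arm

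*Protocol article*

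**What the plan says.** Data collection describes HADS as a 14-item tool with a depression and an anxiety subscale, then states: "This is a kind of categorical scale, and cut-off scores for each subscale are as follows". The cut-offs are: "0 to 7 represents normal, 8 to 10 represents mild, 11 to 14 represents moderate, and 15 to 21 represents severe".

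The table shell in Results has a row "Anxiety subscale" followed by Normal, Mild, Moderate and Severe, the same block for depression, and a P value column. Neither a mean nor a median of the 0-21 score is named.

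Statistical analysis assigns tests by variable type: "The categorical variables and continuous variables are respectively analyzed using independent" t-tests and chi-square tests. Taken word for word, this sends categorical variables to t-tests and continuous variables to chi-square. Significance is a P "value less than .05 indicates that there is statistical significance".

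Study design fixes the size: "This study includes 90 patients with advanced lung cancer", and "each group is assigned 45 patients".

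**The concern.** Four contiguous ranges covering 0 to 21 are a grouping of a score, so the article's own cut-offs contradict the label categorical. The label has consequences, because the test is chosen by variable type.

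Grouping treats unequal changes oddly. A patient who falls from 7 to 2 stays in Normal, while one who falls from 8 to 7 changes band. A Pearson chi-square on the bands also ignores that they are ordered, and spreads the comparison over 3 degrees of freedom.

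Mood is one of the two constructs measured, and worry is one of the three symptoms that the EQUIP sessions address. With 45 patients per arm there is little information to spare.

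**Working it through.** **Inputs from the article.** 45 per arm; significance level 0.05 (sidedness not stated, two-sided taken); bands 0-7, 8-10, 11-14 and 15-21. The article states no power, effect, SD or HADS distribution, so there is no figure of its own to reproduce.

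**Assumptions.** Control mean 6 to 10; SD 4; true reduction of 0.4, 0.5 or 0.6 SD; no dropout; scores rounded and clipped to 0-21; normal, or right-skewed (gamma) as a variation.

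**Step 1, t-test on the score.** Power is approximately Φ(d√(n/2) − 1.96), with √(45/2) = 4.743.
- d = 0.5: Φ(2.372 − 1.96) = Φ(0.41) = 0.66
- d = 0.6: Φ(2.846 − 1.96) = Φ(0.89) = 0.81
- 80% power is reached at d = (1.96 + 0.842)/4.743 = 0.59

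**Step 2, chi-square on the bands, one case by formula.** Control mean 7, effect 0.6 SD, so the treated mean is 7 − 2.4 = 4.6. Cutting the normal curve at 7.5, 10.5 and 14.5 gives:

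| Band | Control p₁ | Treated p₂ | (p₁ − p₂)²/(p₁ + p₂) | Expected per arm, 45(p₁ + p₂)/2 |
|---|---|---|---|---|
| Normal | 0.550 | 0.766 | 0.0355 | 29.6 |
| Mild | 0.260 | 0.164 | 0.0215 | 9.5 |
| Moderate | 0.160 | 0.063 | 0.0420 | 5.0 |
| Severe | 0.030 | 0.007 | 0.0152 | 0.8 |

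The noncentrality is 45 × (0.0355 + 0.0215 + 0.0420 + 0.0152) = 45 × 0.1142 = 5.14. On 3 degrees of freedom this gives power of about 0.45. Simulation gives 0.44, against 0.80 for the t-test.

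**Step 3, simulation over the grid** (20,000 trials per scenario, normal scores, SD 4). Each cell shows t-test power / chi-square power, then the loss in percentage points.

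| Control mean | 0.4 SD | 0.5 SD | 0.6 SD |
|---|---|---|---|
| 6 | 0.45 / 0.19: 27 | 0.65 / 0.28: 37 | 0.78 / 0.38: 40 |
| 7 | 0.46 / 0.21: 25 | 0.64 / 0.31: 33 | 0.80 / 0.44: 36 |
| 8 | 0.46 / 0.23: 23 | 0.64 / 0.35: 30 | 0.80 / 0.48: 32 |
| 9 | 0.47 / 0.25: 22 | 0.64 / 0.38: 26 | 0.80 / 0.52: 27 |
| 10 | 0.46 / 0.27: 19 | 0.64 / 0.40: 24 | 0.80 / 0.55: 25 |

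With skewed scores and the same effects, the loss is 25 to 55 points at means 6 to 8 and 18 to 27 points at means 9 to 10.

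**Step 4, an ordered test on the same bands.** A linear trend test loses less against the t-test: 5 to 23 points over the normal grid above. With skewed scores at means 6 to 8 and effects of 0.5 to 0.6 SD it still loses 24 to 51 points, so using the order recovers only part of what the score holds.

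**Step 5, sparsity** (both distributions, effects 0.4 to 0.6 SD).

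| Control mean | Expected Severe count per arm | Trials with an expected count below 5 |
|---|---|---|
| 6 to 8 | 0.4 to 2.5 | 98-100% |
| 9 | 2.5 to 3.4 | 86-98% |
| 10 | 3.9 to 4.7 | 52-75% |

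**Step 6, false positives.** With no true difference, at means 6 and 8 and both distributions, the chi-square test rejects in 3.7% to 4.7% of trials.

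**The case against.** **Chi-square on the bands is inferred.** The sentence in Statistical analysis literally gives t-tests to categorical variables. This stands: the power comparison applies only if that sentence is a transposition. The literal reading does not rescue the plan, because a t-test needs numbers and the bands are labels, so the sentence has to be corrected either way.

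**The table may hold scores after all.** The anxiety and depression rows above the bands could be meant for a mean; the FACT-L rows carry no label either, and Statistical analysis mentions means and medians in general terms. This also stands in part. A reader might infer that the score will never be reported, but an empty table shell does not settle that. What can be said is that no score summary is named for HADS, while the text calls the scale categorical.

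**The size is assumed.** Correct. No single figure for the power loss can be attributed to this trial, and the range belongs with its assumptions.

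**Sparse cells do not make the test invalid.** A reader might infer from the small Severe counts that the chi-square result would be untrustworthy. The null simulations do not support this: the test is close to nominal or slightly conservative. Nor is a shift in mood invisible to the bands, since a change in the mean moves some patients across the cut-offs; it is detected less often.

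**Conclusion.** The point holds in a limited form. The article labels a 0-21 score categorical against its own cut-offs, and its table shell is built on the four bands without naming a score summary. If the bands are compared by chi-square, the loss of power against a t-test on the score is about 19 to 40 percentage points. That rests on 45 per arm, SD 4, normal scores, control mean 6 to 10 and a difference of 0.4 to 0.6 SD, none of which except the sample size comes from the article. Skewed scores make the loss larger at means 6 to 8 and leave it about the same at 9 to 10.

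The Severe band will usually be sparse, less surely at a mean near 10. The harm is lost power on one of two measured constructs, with no sign of excess false positives. This should be changed, but it does not invalidate the trial.

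**What to change.** 1. In Data collection, describe each HADS subscale as a 0-21 score with four conventional severity bands, and drop the statement that the scale is categorical.
2. In Statistical analysis, state that the anxiety and depression scores are compared between arms as continuous outcomes, with the mean difference and 95% CI. Adjust for the baseline score only if one is collected; the article does not say that it is.
3. In the Results table, add one score row per subscale. Keep the four bands as descriptive counts, or, if they are tested, use an ordinal method such as a trend or Mann-Whitney test.
4. Correct the test pairing so that continuous variables go to t-tests and categorical variables to chi-square tests.

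The cost is wording and two table rows. The scores must exist already in order to assign the bands, so items 1 to 4 need no new data.

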### Statistical analysis

2.5

All the data can be recorded into the software of Microsoft Excel 2013, and the analysis of all the data is carried out through utilizing the software of IBM SPSS Statistics for Windows, version 20 (IBM Corp., Armonk, NY). All the data are represented via the proper characteristics, for instance, median, mean, and percentage. The categorical variables and continuous variables are respectively analyzed using independent *t*-tests and χ^2^-tests. *P* value less than .05 indicates that there is statistical significance.

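### The statistical analysis section pairs the tests with the wrong variable types: t-tests for categorical variables and chi-square tests for continuous ones

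*Protocol article*

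**What the plan says.** The comparison rule stands in Statistical analysis (2.5): "The categorical variables and continuous variables are respectively analyzed using independent *t*-tests and χ^2^-tests". The rest of that section covers software, the significance threshold of .05 and descriptive summaries ("All the data are represented via the proper characteristics, for instance, median, mean, and percentage"). None of it assigns a test to an outcome.

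The outcomes are of both types. Data collection (2.4) describes the quality-of-life instrument: "The 36-item tool measures emotional, physical, social, emotional, functional health and the symptoms specific to lung cancer". In Table 1 (Results) this becomes four well-being domains and "Overall quality of life", five rows without categories and therefore read here as scores. For HADS the same section says "This is a kind of categorical scale, and cut-off scores for each subscale are as follows: 0 to 7 represents normal", followed by the mild, moderate and severe bands. Table 1 shows anxiety and depression by those four bands. The table has a P value column but names no test.

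On size, Study design (2.1) says "All the patients are randomly assigned to the control and intervention group, each group is assigned 45 patients".

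**The concern.** The word *respectively* fixes the pairing by order: first variable type with first test, second with second. That sends the HADS bands to a t-test and the quality-of-life scores to a chi-square test.

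A chi-square test on a score treats each distinct value as an unordered category. It ignores both the order of the values and the distance between them, and with 45 patients per arm it spreads them over many nearly empty columns. The article's objective is the effect on quality of life, and those are the rows where the loss would be greatest. A t-test on severity bands needs a number for each band, and the article gives none.

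At stake is whether the published rule can be followed at all. The analysts must either run unsuitable tests or depart from the only comparison method the article states.

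**Working it through.** **1. Stated pairing against the outcomes.** The article gives no effect size, SD or power, so there is no figure to reproduce. The first check sets the rule beside Table 1.

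| Table 1 outcome | Type | Test as written | Test that fits |
|---|---|---|---|
| Physical, social, emotional and functional well-being; overall quality of life (5) | score | chi-square | independent t-test |
| HADS anxiety and depression bands (2) | four categories | independent t-test | chi-square |

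All 5 + 2 = 7 comparisons are mismatched, counting each HADS subscale once.

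**2. Chi-square on scores: the limiting case.** Suppose all 90 scores differ. Each column then holds one patient, and with equal arms each cell has expected count 0.5. A column contributes (1 − 0.5)²/0.5 + (0 − 0.5)²/0.5 = 1. The statistic is 90 × 1 = 90 on 90 − 1 = 89 degrees of freedom, so P = 0.45 whatever the treatment effect.

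More generally, each cell's expected count is half its column total, so it is below 5 whenever fewer than 10 patients share a score. In most simulated settings 95-100% of cells were in that position; the share was 91% in one bounded setting.

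**3. Chi-square on scores: simulation.** From the article: 45 per arm and a threshold of .05 (taken as two-sided). Assumed: normal scores rounded to integers, and the SDs, bounds and true differences shown. Entries are the proportion of simulated trials with P < .05, from 3,000 trials per row.

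| Score | True difference | Chi-square | t-test |
|---|---|---|---|
| Subscale-like, SD 5, bounded 0-28 | 0 | 0.025 | 0.051 |
| | 0.5 SD | 0.098 | 0.635 |
| | 0.6 SD | 0.154 | 0.806 |
| Total-like, SD 18, bounded 0-136 | 0 | 0.001 | 0.049 |
| | 0.5 SD | 0.004 | 0.641 |
| | 0.6 SD | 0.005 | 0.796 |

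Other assumptions move the chi-square figures a little. With SD 20 for the total they lie at about 0.3-0.6%. With unbounded subscale scores they are about 7% at 0.5 SD and 10% at 0.6 SD.

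As a cross-check on the t-test by normal approximation, power ≈ Φ(d√(n/2) − 1.96):
- d = 0.5: 0.5 × √22.5 = 2.372, and Φ(0.412) = 0.66.
- d = 0.6: 0.6 × √22.5 = 2.846, and Φ(0.886) = 0.81. The exact t calculation gives 0.80.

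**4. t-test on HADS bands.** The bands were coded 0, 1, 2, 3. The codes and the band proportions (normal, mild, moderate, severe) are assumptions; 5,000 trials per row.

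| Arm 1 | Arm 2 | t-test on codes | Chi-square |
|---|---|---|---|
| .50/.25/.15/.10 | the same | 0.051 | 0.049 |
| .65/.20/.10/.05 | .40/.25/.20/.15 | 0.734 | 0.568 |
| .25/.50/.20/.05 | .50/.20/.10/.20 | 0.061 | 0.930 |

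The t-test keeps its type I error. It does better than chi-square for a plain shift between bands, and it misses a difference that leaves the mean code nearly unchanged (last row: mean codes 1.05 and 1.00).

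**The case against.** The strongest reply is that this is a slip of word order. The two tests named are the usual pair for the two variable types in Table 1, the English is rough elsewhere (the description of the quality-of-life instrument lists the emotional domain twice), and a competent analyst would probably run the right tests. That is likely, and it lowers the expected harm: the loss of power arises only if the sentence is followed to the letter. It does not make the sentence right. The sentence is complete and grammatical, so faulty text extraction does not explain it, and no other part of the article overrides it. A separate statistical analysis plan may state the tests correctly, but it would then contradict this article.

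A reader might infer that every test in Table 1 would be invalid or would produce false positives. The documents and the figures above do not support that. With no true difference, chi-square on raw scores rejects in only about 0.1-2.5% of simulated trials, which is conservative. The t-test on coded HADS bands rejects in about 5%. The tests are mismatched to the variable types; they do not inflate the type I error.

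A reader might also conclude that the analysis should adjust for baseline or treat HADS scores as continuous. Neither follows from this error. The article describes no baseline measurement, Table 1 shows HADS only by band, and an unadjusted t-test is valid in a randomised trial.

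**Conclusion.** The point stands as an error in a stated rule: the two tests are assigned to the wrong variable types, and all seven comparisons in Table 1 are affected. The pairing itself can be read directly from the text and needs no assumption.

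The size of the consequence does rest on assumptions, because the article gives no SD or effect size. At a true difference of 0.5 to 0.6 SD, the literal rule cuts the chance of detecting a quality-of-life effect from about 63-81% to about 7-15% for a subscale-like score and to under 1% for a total-like score. The exact percentages shift with SD and score bounds; the direction does not. For HADS the fault is mainly that the test cannot be run without codes that the article does not define. With codes 0-3 it would answer a question about mean code rather than about the distribution over bands.

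**What to change.** Swap the test names in the one sentence of Statistical analysis (2.5). For example: continuous variables (the quality-of-life scores) are compared between arms by independent t-tests, and categorical variables (the HADS severity bands) by chi-square tests, with an exact test where expected counts are small. With 45 per arm, a band holding fewer than 10 patients in total already has expected counts below 5, so the last clause may well be needed for the severe band.

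If a separate statistical analysis plan exists, check that it states the same pairing. The change costs one sentence, affects neither sample size nor data collection, and has no downside.

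### FACT-L scores are to be compared by an unadjusted t-test; with 45 patients per arm, adjusting for a baseline score would be more precise

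*Protocol article*

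**What the plan says.** The analysis method is one sentence in section 2.5 (Statistical analysis): "The categorical variables and continuous variables are respectively analyzed using independent *t*-tests and χ^2^-tests". Outcomes are thus "analyzed using independent *t*-tests" or chi-square tests, and no covariate, change score or repeated-measures model is named. Read word for word, it gives t-tests to categorical variables and chi-square tests to continuous ones. The intended meaning must be the reverse, and the sentence needs correcting in any case.

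The results shell in section 3 is titled "Patient's life quality and HADS in both groups". It has one column per arm and a P value. FACT-L appears as four well-being domains and an overall score. HADS appears as four severity bands (normal to severe) for each subscale. There is no baseline, follow-up or change column.

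Section 2.1 gives the size: "This study includes 90 patients with advanced lung cancer", and "each group is assigned 45 patients". Section 2.4 describes a 36-item FACT-L and a 14-item HADS. It mentions neither a baseline measurement nor an assessment time. Section 2.3 says of the sessions, which only the intervention arm receives: "The EQUIP courses arrangement is consistent with the existing outpatient chemotherapy or clinic visits time".

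**The concern.** Section 2.2 admits stage 3 and stage 4 patients up to 8 weeks after diagnosis, so quality of life is likely to vary considerably at entry. An unadjusted comparison leaves all of that between-patient spread in the standard error. With 45 per arm this matters, and the article gives no target difference, SD or power for its 90 patients, so it offers no evidence that precision can be spared.

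A baseline score usually explains part of the follow-up score, and conditioning on it removes that part of the variance. The baseline must be taken before randomisation and cannot be recovered once patients are enrolled, so the decision has to be made early.

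**Working it through.** The article gives no power figure to reproduce, so the stated design is evaluated first and the adjusted analysis is set against it.

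**Inputs from the article.** n = 45 per arm (section 2.1); significance level .05 (section 2.5), taken as two-sided because the article does not say.

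**Assumptions.** Baseline to follow-up correlation r = 0.3, 0.5 or 0.7; a true difference of 0.5 SD for the power comparison; complete data on all 90 patients.

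**Step 1: unadjusted t-test.** The standard error in SD units is sqrt(2/45) = 0.2108. By the normal approximation, the difference detectable with 80% power is (1.960 + 0.842) × 0.2108 = 0.591 SD. The noncentral t with 88 degrees of freedom gives 0.597 SD. At a true 0.5 SD, the noncentrality is 0.5 / 0.2108 = 2.372 and the power is 0.650.

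**Step 2: ANCOVA on the baseline score.** The residual SD is SD × sqrt(1 − r²). The detectable difference is therefore 0.597 × sqrt(1 − r²), the noncentrality is 2.372 / sqrt(1 − r²) with 87 degrees of freedom, and the equivalent unadjusted sample is 45 / (1 − r²) per arm.

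| r | Residual variance (1 − r²) | Detectable difference, 80% power | Power at 0.5 SD | Equivalent n per arm, t-test |
|---|---|---|---|---|
| none (t-test) | 1.00 | 0.597 SD | 65.0% | 45 |
| 0.3 | 0.91 | 0.597 × 0.954 = 0.57 SD | 69.1% | 45 / 0.91 = 49 |
| 0.5 | 0.75 | 0.597 × 0.866 = 0.52 SD | 77.3% | 45 / 0.75 = 60 |
| 0.7 | 0.51 | 0.597 × 0.714 = 0.43 SD | 90.7% | 45 / 0.51 = 88 |

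**Step 3: sample size for 80% power at 0.5 SD.** By the normal approximation, 63 per arm are needed unadjusted and 48 per arm with r = 0.5. The planned 45 falls well short of the first figure and just short of the second.

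**Scope.** These figures apply to the FACT-L scores. On the intended reading, the banded HADS results go to a chi-square test, and a difference in SD units does not describe that comparison.

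**The case against.** The strongest reply is that the t-test is not wrong. Under randomisation it is unbiased, it holds its type I error, and its standard error already allows for chance imbalance at baseline. That stands: the point is efficiency, not validity.

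A second reply is that this is a condensed article. Covariates are often left to an analysis plan, and an outcome table without a baseline column does not prove that baseline scores are not collected. The part about collection stands, which is why the fix says to add the baseline only if it is not already taken. The part about covariates is weaker, because the article does state its tests and lays out its table, and both describe an unadjusted comparison.

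Third, the size of the gain rests on an assumed correlation. This also stands. At r = 0.3 the gain is only about 4 percentage points of power. Deaths and dropout would lower power under either analysis.

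A reader might go further and infer that the arms are measured at different times, because the four sessions float with each patient's visits and controls have no fourth session. The article does not support that. No section ties assessment to session four. Section 2.3 puts the evaluations in the hands of a separate coordinator who does not know the allocation, and such a person could not readily trigger assessments from a session held in one arm only. Patients in both arms also receive routine care. Unequal timing is a possibility left open and not a feature of the plan.

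**Conclusion.** The point holds as one of precision. On the evident reading of section 2.5, FACT-L scores are compared by a valid but inefficient unadjusted t-test. Baseline adjustment would lower the detectable difference from about 0.60 SD to between 0.57 and 0.43 SD. Power at 0.5 SD would rise from 65% to between 69% and 91%. Those ranges assume correlations of 0.3 to 0.7, a two-sided .05 level and complete data; the article gives neither the correlation nor an expected effect.

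The result should not be read as biased because of the t-test, and the figures do not extend to the HADS bands. The remark on timing is secondary and conditional. Baseline adjustment would not cure unequal timing if it occurred, whereas a common assessment time counted from randomisation would rule it out.

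**What to change.** 1. Correct the sentence in section 2.5 so that t-tests go with continuous variables and chi-square tests with categorical ones.
2. Take FACT-L and HADS before randomisation, if this is not already done.
3. Compare FACT-L scores by ANCOVA with the baseline score as covariate, and report the adjusted mean difference with its 95% CI. Add a baseline column to Table 1.
4. Keep the HADS bands as tabulated. If wanted, add ANCOVA on the HADS subscale scores alongside them.
5. State one follow-up time, counted from randomisation and the same in both arms.

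The cost is a change of wording and table layout plus, where no baseline is yet taken, one questionnaire of 36 + 14 = 50 items per patient. A follow-up time counted from randomisation may not always coincide with a routine visit. This has some tension with the aim in section 2.3 of sparing patients inconvenience.
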